**Fig. 1 Fig1:**
[figure not shown]
CONSORT flow diagram

### Inclusion criteria

Aged 18 years or more.Own a mobile phone or landline phone that can receive SMS text messages.Able to understand English sufficiently to complete the study procedures.People who have lost at least 5 % of their starting weight at the end of their weight loss programme. The initial screen for 5 % weight loss is based on self-reported weight at the baseline screening call and is later verified objectively at the baseline home visit. Because we anticipate there is likely to be variation in participants self-reported weight using their home scales and the calibrated scales used by researchers at the home visit to verify percentage weight loss, the decision was made to allow some flexibility in the inclusion criteria at the home visit and include people who were confirmed to have lost at least 4 %.

### Exclusion criteria

Women who are known to be pregnant or intending to become pregnant during the study.

### Comparator group

The comparator group receive the standard Lighten Up maintenance leaflet which consists of a list of tips that may help people to maintain their weight under the main headings of: “Managing your thoughts and any slip ups, planning, shopping, eating behaviour, support, coping with social occasions and rewards”. Participants will also receive a diagram representing healthy diet composition and a list of websites related to weight management.

### Intervention group

The intervention group receive support telephone calls at weeks zero, two and four that encourage daily self-weighing, recording of weight on a record card, setting a weight target together with regular reminder SMS text messages. The telephone calls aim to encourage and provide minimal behavioural intervention to support participants to weigh themselves daily and record their weight on the weight record card, which are given to participants at the initial baseline visit.

#### Intervention components

The goal of the intervention will be for participants to make a commitment to avoid regaining more than 1 kg of their baseline weight. The main element used to achieve both goal setting and the monitoring necessary to ensure this, is support telephone calls at weeks zero, two and four, that encourage target setting and daily self-weighing, together with reminder text messages three days per week for the first four weeks, reducing to twice weekly thereafter. We have purposefully designed the intervention such that the telephone contacts and frequent texts messages occur in the first four weeks because the period after initial weight loss is when people are at highest risk of weight regain [5]. We also wanted to maximise the possibility that regular self-weighing becomes a habit for participants. Table 1 details the behaviour change techniques used based on the CALO-RE Behaviour Change Taxonomy [14].

**Table 1 Tab1:** Intervention components using the CALO-RE behavioural change taxonomy [14]

Behavioural technique	Definition
*Goal setting (outcome)*	Telephonists encourage participants to set a weight goal for regain such as ‘*In a year I aim to weigh no more than I do now’.*
*Prompt review of outcome goals*	Participants will be instructed to remain within 1 kg of their study baseline weight and to review their weight each day against this target.
*Provide information on the consequences of behaviour in general*	Telephonists discuss the benefits of self-weighing with the participant.
*Environmental restructuring*	The telephonist encourages the participant to cue this behaviour ‘*move the scales into your bathroom so when you see them after your shower it will remind you*’.
*Provide information on where and when to perform the behaviour*	The telephonist asks participants to describe when and where the weighing will take place. Participants will be encouraged to weigh themselves at the same time every day.
*Use follow-up prompts*	Participants receive telephone calls at weeks zero, 2 and 4 that encourage daily self-weighing, together with reminder text messages every other day for the first four weeks, reducing to twice weekly thereafter.
*Barrier identification/ Problem solving*	The telephonists offer practical solutions and give participants ideas and strategies to overcome barriers to daily self-weighing. Participants will be advised that if their current weight is more than 1 kg above target weight then they would be best to restart following the plan they followed for eating and physical activity when they were on their weight loss programme.
*Agree behavioural contract*	The telephonist asks participants if they can commit to a weight change target and to daily weighing.
*Provided general encouragement*	The telephonist encourages the participant ‘*remember every time you record your weight you are one step nearer to this becoming a healthy habit’*’
*Prompt self-monitoring of behavioural outcome*	Participants will be advised to weigh themselves daily and record it on the record card provided
*Prompt social support*	Prompt participants to ask someone they care about to support them. Participant are advised to tell this person their goal and ask them to remind the participant of this goal and check commitment to it and whether it has been achieved every week.

#### Telephone calls

The telephonists will call participants three times; at weeks zero, two and four of the intervention. The calls will be about five minutes each. The aim of the intervention is to prevent participants regaining more than 1 kg, however we recognise that some participants will want to continue to lose weight and we will advise participants to set a weight loss goal for 12 weeks. If participants wish to continue to lose weight we will advise these participants to aim to lose 1–2lbs per week as in line with national guidance [15]. Participants will be encouraged to weigh themselves at the same time every day wearing similar amounts of clothing or no clothing. The telephonist explains that the aim of weighing frequently is to check themselves against the target weight set. The telephonist will ask participants to write their target weight on their record card provided and explain that every day the participant should check their recorded weight against the target weight. The telephonist will encourage the participant and advise them that if their current weight is more than 1 kg above their weight at the end of their weight loss programme then they should restart following the plan they followed for eating and physical activity when they were on their weight loss programme.

#### Week two and four calls

The telephone calls in weeks two and four will include a review of how participants are getting on compared to their target weight, the frequency of self-weighing and the recording of weight over the previous weeks. Those not weighing themselves daily will be asked about barriers to this and the telephonist will help with practical solutions/ideas and strategies of how they might overcome them. Participants will be further encouraged to self-weigh daily. The importance of using the weight record to compare their weight to their goal will be emphasised, as well as engaging in regular physical activity/healthy eating. The aim is to suggest to participants that daily weighing is a healthy habit to help them manage their weight and that they should adopt this for the rest of their life. Apart from these scheduled calls, participants are not able to telephone the call centre to receive further support.

### SMS text messages

Automated reminder SMS text messages will be sent three times per week for the first four weeks, reducing to twice weekly for eight more weeks. The goal for the intervention is to encourage self-weighing such that it becomes a habit to prevent weight regain. We will send reminder texts twice per month as a ‘top up’ strategy after the 12 week intervention until 12 months follow-up. Participants cannot reply to the texts and they provide no tailored or interactive component.

#### Delivery of the intervention

Gateway Family Services are a triage centre for weight management services on behalf of Birmingham Public Health Directorate, England. The Gateway call centre is staffed by employees who are trained in call centre management systems and customer relations, but not in nutrition or weight management. Call centre staff do not offer any opinions or undertake any motivational interviewing, but they listen, offer positive reinforcement about regular self-weighing and setting weight goals, offer advice about intention implementations, give encouragement and pass on factual information. Call centre staff will be given a detailed intervention manual from the University research team and will be given up to five practice calls to enable simulation of intervention calls and for the research team to provide feedback about different methods to communicate to people about their weight. The University research team will also be available if any queries arise throughout the trial.

### Primary outcome

The difference between the groups in weight change from baseline to 12 months follow-up.

### Secondary outcomes

The proportion of participants in the intervention and comparator group who have regained less than 1 kg in weight at three and 12 month follow-up.The difference between groups in weight change from baseline to three months follow-up (i.e., end of behavioural support for weight maintenance).The cost to the NHS per kg, and per kg/m [2], of the additional weight loss maintained for the intervention compared to comparator group at 12 months, the cost per quality adjusted life years (QALY) during the intervention period and predicted lifetime QALYs gained.To assess the effects of the intervention on uncontrolled eating, emotional eating and weight preoccupation at three and 12 months follow-up.

### Non-efficacy outcomes

The difference in frequency of self-weighing in the comparator and intervention groups at three and 12 months.Using items from the three factor eating questionnaire we will examine if there are differences in cognitive restraint of eating and frequency of self-weighing at three, six and 12 months [16].Dose–response of frequency of self weighing on weight change at three and 12 months.The association between automaticity (measured by HABITS index) and frequency of weighing and the association of weight change and automaticity at three and six months follow-up.

### Assessments

#### Baseline

A researcher measures participant’s height and weight at a home visit before randomisation. Participants complete the baseline questionnaire and answer the open ended questions about their previous weight loss attempts and strategies they use to control their weight before being randomised. As a process measure the intervention group will be given a set of BodyTrace scales to use to weigh themselves, these scales transmit weight data to a remote database to provide an objective measure of weighing frequency (see below).

#### Three and 12 month follow-up

Participants will be mailed the follow-up questionnaire prior to being contacted to arrange a visit by the research team. At each visit the questionnaire is collected and participants will be weighed by the researchers. Participants will be given a £20 high street shopping voucher for completing each follow-up.

#### Six month follow-up

Participants will be sent the six month questionnaire and a self-addressed envelope to return in the post.

### Process measures

We are collecting process measures to monitor recruitment, intervention delivery and potential variables that may mediate the outcomes. Our hypothesis is that self-weighing leads to the development of conscious cognitive restraint, which the National Weight Control Registry has found to be a key behavioural attribute associated with weight maintenance [17]. Using six items from the revised three factor eating questionnaire [16] we will examine if feedback from self weighing has led to development of conscious cognitive restraint of eating (measured in both groups) at three, six and 12 months post randomisation. In the intervention group we will use seven items from the index of habit strength [18] to measure the automaticity of self-weighing and five items from Steinberg [12] to measure perceptions of daily self weighing at the same follow-ups. At three, six and 12 months follow up participants in both groups will be asked to complete a series of open ended questions about any weight control practices they may have used in the previous two weeks, which will be coded. Within these questions we will specifically ask participants whether they have reapplied any behavioural techniques they acquired through participation in their weight loss programme and whether they have re-enrolled in a weight loss programme. We will then be able to examine whether the intervention may work by encouraging people to reapply lessons and techniques they learnt on the weight loss programme or it works by encouraging participants to enrol in a weight loss programme once more. Table 2 documents the process measures collected.

**Table 2 Tab2:** Measurements and study questionnaires at baseline and follow-ups

Reach		
Number of participants eligible		
Number of participants consented		
Number of participants consented and randomised		
Intervention		
	Comparator group	Intervention group
Frequency of recording self-weighing –record cards		X^a^
Frequency of self-weighing (objective scales)		X
Psychological Measures		
Index of habit strength [18]		X
Energy restriction [16]	X	X
Perceptions of self-weighing [20]		X
Thoughts about regular weighing (open ended questions)		X
Weight locus of control [21]	X	X
Weight loss strategies		
Weight control strategies (including frequency of self-weighing) [22]	X	X
Attendance at commercial weight loss programmes & application of skills learnt at weight loss programme (open ended)	X	X
Open ended questions asked if participants are no longer managing their weight.	X	X
Intervention delivery of phone calls		X^a^

^a^3 month follow-up only

One weakness of previous trials is that self-weighing frequency was based on self-report rather than objective measures. Here we use Body Trace scales (http://www.bodytrace.com/) which use mobile phone signals to send the weight of the participant to a central database in real time. This will provide an objective measure of the weighing frequency of intervention participants and allow us to examine adherence to the daily weighing intervention.

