### Randomisation

The randomisation list will be developed by an independent statistician within the Primary Care Clinical Research and Trials Unit using NQuery Advisor. Participants will be randomised to the intervention or comparator groups on a 1:1 basis using random permuted blocks of varying size. Some people who have lost weight will want to continue attending the weight management group and pay themselves, after completing the NHS-provided 12 week course, and this is likely to have an important effect on weight at 12 months. To ensure this effect is balanced by treatment arm we will stratify randomisation by whether participants intend to continue with their weight loss programme or not.

Participants will be randomised at the baseline appointment after consent is gained and eligibility checked. The research assistants will be operating in participants’ homes and out of office hours so the only option available will be to implement randomisation by opaque sealed envelopes. These will be sequentially numbered and research assistants open these in sequence and the trial manager checks their adherence to this instruction regularly.

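### A two-week look-back at 3, 6 and 12 months gives point prevalence of re-enrolment, not exposure over the year, so the mechanism comparison is made with substantial error

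*Protocol article*

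**What the plan says.** The Process measures section sets the timing and arms ("At three, six and 12 months follow up participants in both groups") and then the content: "open ended questions about any weight control practices they may have used in the previous two weeks, which will be coded". The next sentence puts two specific items inside that block: "Within these questions we will specifically ask participants whether they have reapplied any behavioural techniques they acquired through participation in their weight loss programme", and also "whether they have re-enrolled in a weight loss programme".

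The purpose follows directly: "We will then be able to examine whether the intervention may work by encouraging people to reapply lessons and techniques they learnt" on the programme, or whether it works instead by leading them to enrol again. The section on analysis of process measures plans a mediation analysis.

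Table 2 has one row, for both arms, that combines attendance at commercial programmes with use of skills learnt there. It shows no look-back. No other attendance record with a longer window is described.

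Table 1 explains why these behaviours may come and go. Participants more than 1 kg above target are advised to "restart following the plan they followed for eating and physical activity when they were on their weight loss programme".

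**The concern.** A two-week window suits a description of current behaviour. It suits less well an event that can start and finish between assessments. Someone who joins a 12-week course in week 30 and completes it in week 42 is outside all three windows. If the two-week frame applies to the re-enrolment item, that person is recorded as not having re-enrolled, although the course falls in the half-year before the primary outcome.

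At stake is the comparison the protocol sets out to make between two routes by which the intervention could work. Three snapshots give the share of each arm attending at those times. They do not give the share that attended at any time, or for how long, and that is the exposure relevant to weight change over 12 months. Detection also depends on how long an episode lasts, so short attendances are missed more often than full courses.

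**Working it through.** The protocol states no coverage or detection figure, so there is none to reproduce.

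**Inputs from the protocol**
- Look-back of 2 weeks; assessments at 3, 6 and 12 months (Process measures).
- Course length of 12 weeks (Design; Considerations for future research).

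**Assumptions**
- Assessments fall at weeks 13, 26 and 52, so the windows are weeks 11–13, 24–26 and 50–52.
- The two-week frame applies to the re-enrolment item.
- Start dates are uniform over weeks 0–52.
- The 2-, 4- and 24-week lengths are illustrations; the protocol gives no such figures.

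**Step 1: coverage.** 3 × 2 = 6 weeks, and 6/52 = 11.5%. The remaining 46/52 = 88.5% lies outside the windows. The longest gap runs from week 26 to week 50, which is 24 weeks.

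**Step 2: detection.** An attendance of L weeks starting at week s overlaps a window ending at week w if w − 2 − L < s < w. Taking the union over w = 13, 26 and 52:

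| L (weeks) | Starts that are detected (weeks) | Detected | Missed |
|---|---|---|---|
| 2 | 9–13, 22–26, 48–52 | 12/52 = 23% | 40/52 = 77% |
| 4 | 7–13, 20–26, 46–52 | 18/52 = 35% | 34/52 = 65% |
| 12 | 0–26, 38–52 | 40/52 = 77% | 12/52 = 23% |
| 24 | 0–52 | 52/52 = 100% | 0% |

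Every missed 12-week course starts in weeks 26–38.

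**Step 3: how far this depends on the assumptions.**
- Starts in weeks 0–26 only: 12-week courses 26/26 = 100%; 4-week attendances 12/26 = 46%.
- Starts in weeks 26–52 only: 14/26 = 54% and 6/26 = 23%.
- Attendance must end by week 52: 28/40 = 70% and 14/48 = 29%.
- Six-month postal form not returned: 27/52 = 52% and 12/52 = 23%.

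**Step 4: effect on the between-arm comparison.** Suppose nobody reports a re-enrolment that did not happen and detection is the same in both arms. Then:

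observed difference in the share ever re-enrolled = detection × true difference.

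The observed difference would be 0.77 of the true one if all attendances lasted 12 weeks, and 0.35 of it if all lasted 4 weeks. If typical length differs by arm, detection differs too. At equal true shares, an arm with 4-week attendances would show 18/40 = 45% of the share seen in an arm with 12-week courses. That would be a bias and not simple attenuation.

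**The case against.** The strongest objection is that the two-week limit on re-enrolment is inferred. The phrase is attached to weight control practices. The re-enrolment item has no window of its own, and neither does the Table 2 row. If participants are simply asked whether they have re-enrolled, someone who did so in month 7 could answer yes at 12 months. The questionnaire is not shown. This stands as a caveat: the placement inside the two-week questions makes the limit the natural reading, but not a stated fact.

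Secondly, a reader might infer that the mechanism question cannot be answered at all. The documents do not support that. Both arms get the same questions at the same times, most 12-week courses are caught, and all of those begun in the first half-year are. The protocol itself treats the period soon after weight loss as the time of highest risk; if re-enrolments cluster there, detection of full courses exceeds 77%. The protocol also claims only to examine whether the intervention may work this way, in analyses it describes as likely.

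Thirdly, a reader might link this to the Randomisation section, which says of continued attendance that "this is likely to have an important effect on weight at 12 months". That remark concerns people who carry on at their own expense after the funded course. Intention to do so is handled by stratification, adjustment and a planned subgroup analysis. It is not a statement about later re-enrolment.

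Fourthly, a reader might infer that repeat courses would drop out of the secondary outcome that begins "The cost to the NHS per kg". That would follow only if these answers were the sole source of attendance data. The article does not say so, and details of resource-use collection are commonly left to the full protocol.

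Finally, short recall is a defensible choice for everyday behaviour such as reusing techniques. That stands, and the fix below leaves that item alone.

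**Conclusion.** The point holds as one of measurement. On the natural reading, the two items measure point prevalence at three times. Under uniform starts, about 23% of 12-week courses and 65% of 4-week attendances would be missed. The comparison of re-enrolment with reapplied techniques would then carry substantial error, probably towards no effect, though the direction is not assured if episode length differs between arms.

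The percentages rest on the assumed start dates and lengths. The 24-week gap between the six-month assessment and the 12-month window does not depend on start dates or lengths, only on the two-week frame applying. The 11.5% coverage should not be read as a detection rate.

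The damage is confined to a process analysis. The primary outcome, its analysis and the sample size are unaffected.

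**What to change.** 1. Keep the two-week window for current weight control practices and for reapplied techniques.
2. In both arms, ask about re-enrolment or attendance at any programme, commercial or NHS, *since your last study questionnaire*. Ask for approximate weeks attended and whether the place was publicly or self funded.
3. Use this item as the re-enrolment measure in the process analysis. State there that re-enrolment is then cumulative while technique use remains a snapshot, so that their relative strength is read with that difference in mind.
4. If the two-week frame was never meant for the re-enrolment item, correct the Process measures text to say so and give the look-back actually used.

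The cost is a change to one item in questionnaires that both arms already receive. When all forms are returned, the three look-backs (0–3, 3–6 and 6–12 months) cover the whole year. The downside is recall error over up to six months, or up to nine (months 3 to 12) if the six-month form is not returned. That should be modest for an event as memorable as joining a programme.
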